#### **9.5.13 Laboratory tests**

The laboratory tests collected are based on the descriptive series of critically ill patients already published on COVID-19, mostly from China and Italy, and on the usual tests collected during the treatment of acute respiratory distress syndrome (ARDS) associated with infection or sepsis.

#### **9.5.14 Premature discontinuation of trial treatment**

The treatment will be delivered as a single administration of convalescent plasma. In case of severe adverse reaction during the administration (specifically hemodynamic shock), the study plasma will be stopped, and the adverse event described and collected.

If for any reason the treatment is either not administered or prematurely stopped, the patient will remain in the trial for the intention to treat analysis.

No cross-over will be allowed.

| Procedures*                          | Visits    |           |                 |      |      |      |               |     |      |
|--------------------------------------|-----------|-----------|-----------------|------|------|------|---------------|-----|------|
|                                      | Screening | Inclusion | Treatment Phase |      |      |      | Follow Up     |     |      |
|                                      |           | D1        | D7              | D14  | D21  | D28  | ICU Discharge | D90 | D365 |
| Informed consent                     |           | x         |                 |      |      |      |               |     |      |
| Eligibility assessment               | x         | x         |                 |      |      |      |               |     |      |
| Randomisation                        |           | x         |                 |      |      |      |               |     |      |
| Medical history                      |           |           |                 |      |      |      |               |     |      |
| Comorbidities                        |           | x         |                 |      |      |      |               |     |      |
| Prior medications                    |           |           |                 |      |      |      |               |     |      |
| APACH II score                       |           | x         |                 |      |      |      |               |     |      |
| SOFA score                           |           | x         | x               | x    | x    | x    |               |     |      |
| WHO disease progression scale        |           | x         | x               |      |      |      | x             |     |      |
| CRP                                  |           |           |                 |      |      |      |               |     |      |
| Viral load (NP or tracheal PCR)      |           | x         | x               | x    | x    | x    |               |     |      |
| Clinical frailty scale               |           | x         |                 |      |      |      |               |     |      |
| Concomitant drugs against SARS-CoV-2 | x         | x         | x               | x    | x    | x    |               |     |      |
| Biological findings                  |           | x *a      | x *b            | x *b | x *b | x *b |               |     |      |
| 24h-diuresis                         |           | x         | x               | x    | x    | x    |               |     |      |
| Serum sample for central analysis    |           | x         | x               |      |      | x    |               | x   |      |
| Mechanical ventilation               |           | x         | x               | x    | x    | x    |               |     |      |
| Renal replacement therapy            |           | x         | x               | x    | x    | x    |               |     |      |

|                                           |  |   |   |   |   |   |  |   |   |
|-------------------------------------------|--|---|---|---|---|---|--|---|---|
| Vasoactive drugs                          |  | x | x | x | x | x |  |   |   |
| ECMO                                      |  | x | x | x | x | x |  |   |   |
| Nosocomial infections                     |  | x | x | x | x | x |  |   |   |
| Iatrogenic events                         |  | x | x | x | x | x |  |   |   |
| Adverse events &
Serious adverse event |  | x | x | x | x | x |  |   |   |
| ADL scale                                 |  | x |   |   |   |   |  | x | x |
| Anxiety-depression scale                  |  |   |   |   |   |   |  | x | x |
| EQ-5D-5L scale                            |  | x |   |   |   |   |  | x | x |

\* Please see section 9.5 for more details

a. Haemoglobin, Haematocrit, Platelet count, White blood cells count, Neutrophil, Lymphocyte, PaO2, FiO2, Na, K, urea, creatinin, protein, bilirubin, ferritin, CRP, Ddimer, fibrinogen, LDH, TGO, TGP, CPK

b. creatinin, platelet count, bilirubin, CRP, WBC count, Ferritin, Lymphocyt count

## **9.6. Efficacy and Safety Variables**

### **9.6.1 Efficacy and Safety Measurements Assessed and Flow chart**

Measurements will be performed by the investigators and clinical research assistants during their stay in the hospital and during medical visits at each time of endpoints (days 7, 14, 28, 90) in case of hospital discharge, and by phone for day 365 endpoint.

Vital status, dependence on the ventilator and clinical and biological data to calculate the SOFA score will be collected from the patient's record. Viral load, expressed as cycle threshold, will be assessed from tracheal aspirates or naso-pharyngeal swabs and RT-PCR assessment by the usual technique of the routine laboratory. Adverse events possibly related to study intervention will be collected prospectively, according to definitions of iatrogenic events, transfusion-related events and nosocomial infections by the investigator and the clinical research assistant in charge of the study. Scales assessing functional state, psychological state and quality of life will be collected at day 90 visit and over the phone at day 365 visit by a clinical research assistant dedicated to this task by the coordinating center. The adverse events will be collected and severity rating according to Belgian guidelines.

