| Number of study centers : 16                                                                                                                                                                                                                                                                                                                                                                                                                                                                                                                                                                                                                                                                                                                                                                                                                                                                                                                                                                                                                                                                                                                                                                                                                                                                                                                                                                              |                |

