### 7.3. Endpoints

The principal endpoint will be vital status (dead/alive) at day 28

The secondary endpoints will be

- day-90 mortality
- number of ventilator-free days at day 28
- number of renal replacement therapy-free days at day 28
- number of vasopressors-free days at day 28
- use of ECMO before day 28
- value of the SOFA score at days 7, 14 and 28 [1] (see appendix A).
- changes in SOFA scores over the following 7, 14 and 28 days
- value of the SARS-CoV-2 viral load, expressed as cycle threshold, [2] in the tracheal aspirates (for intubated patients) or nasopharyngeal swabs (for extubated patients) at days 7, 14 and 28
- blood C reactive protein (CRP) concentrations at days 7, 14 and 28
- length of stay in the acute care hospital
- location of the patients at day 90: acute care hospital, post-acute care hospital, long-term residency, home
- WHO progression scale prior transfusion, at day 7 and at discharge (see appendix B)
- Hospital Activity of Daily Living (ADL) functional score at day 90 and at day 365. [3] (see appendix C).
- Anxiety-depression evaluation scale at day 90 and at day 365. [4] (see appendix D ).
- Quality of life scale (EQ-5D-5L) at day 90 and at day 365. [5] (see appendix E).
- Transfusion-related adverse events within 7 days
- Sero-positivity to SARS-CoV-2 at days 1, 7, 28 and 90
- Adverse events related to standard of care (mechanical ventilation, prolonged decubitus, prone positioning...) such as:
  - o Ventilator associated pneumonia
  - o Secondary bacteremia [6]
  - o Deep vein thrombosis and pulmonary embolism
  - o Pressure ulcers, stage 2 to 4 (*i.e.* loss of skin, of tissue or of bone) [7]
  - o Ventilator induced baro-traumatism (pneumothorax, pneumo-mediastinum, sub-cutaneous emphysema) [8]
  - o Accidental ablation of tracheal or vascular device [9]
  - o Ventilator induced baro-traumatism (pneumothorax, pneumo-mediastinum, sub-cutaneous emphysema) [8]
  - o Accidental ablation of tracheal or vascular device [9]

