### **9.5.3 Process of randomization**

The process of randomization will be performed through a standard randomization system (UCL clinical trial center, Pr [name]) either directly through the eCRF system or by the CCC St Luc. The randomization process will be stratified according to the delay from tracheal intubation to inclusion (" $\leq$  48 hours"; "between 48 hours and 5 days"). A response to telephone calls for any issue regarding the inclusion criteria will be available 24/7 (see "availability of the study product" paragraph).

The treatment (intervention versus control) will be allocated in 2 arms in a 1:1 ratio. The randomization table will be made of permuted block size provided by the statistician.

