#### **9.5.4.3 Assessments visits D7 (+-1 day)**

- SOFA score calculation
- Glasgow coma score

- Peep level
- Plateau pressure
- tidal Volume
- Respiratory rate
- FiO2
- PaO2
- PaCO2
- Mean arterial pressure
- Inotropic or vasopressor support for at least one hour
  - Dopamine,
  - dobutamine,
  - noradrenaline < 0,1 µg/kg/min
  - noradrenaline > 0,1 µg/kg/min,
  - adrenaline <0,1 µg/kg/min,
  - adrenaline > 0,1 µg/kg/min,
  - vasopressin/-analogues
- Creatinine
- 24 h diuresis
- Platelet count
- Bilirubin
- CRP
- WBC count
- Ferritin
- Lymphocyte count
- Tracheal aspirate for SARS-CoV-2 viral load, expressed as cycle threshold, assessment
- WHO progression scale
- Total and neutralizing antibodies to SARS-CoV-2 (centralized)

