Regarding the secondary endpoints, quantitative values between groups will be compared by Student t-test or non-parametric Wilcoxon for the SOFA score (at different time points), viral load of SARS-CoV-2 (at different time points), circulating CRP (at different time points), ADL score at day 90, anxiety-depression scale at day 90, sero-conversion. Poisson regression analysis will be considered to analyse number of ventilator-free days up to day 28. Comparison of proportions will be applied to compare location of patient at day 90, as well as presence of various adverse events. If descriptive analysis revealed the presence of potential confounding factors, appropriate multivariate analysis will then be considered.

The two-sided level of significance used in this trial is 5%. Statistical analyses will be carried out using SAS (version 9.4 for Windows) statistical package.

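### Viral load is a raw cycle threshold from each site's routine RT-PCR, compared without a laboratory term: the test stays valid but may lose avoidable precision

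*Protocol*

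**What the plan says.** Section 7.3 defines the endpoint as the "value of the SARS-CoV-2 viral load, expressed as cycle threshold", in tracheal aspirates or nasopharyngeal swabs, at days 7, 14 and 28. It is the value at each visit, not a change from day 1 and not a number of copies. Section 9.6.1 says how it is measured: "RT-PCR assessment by the usual technique of the routine laboratory". The synopsis gives "Number of study centers : 16". Antibody testing is handled differently: the visit lists in 9.5.4 mark it as done centrally.

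For secondary endpoints, section 9.9 says that "quantitative values between groups will be compared by Student t-test or non-parametric Wilcoxon", and the list of variables includes "viral load of SARS-CoV-2 (at different time points". No laboratory or centre term is named. The one route to adjustment there is conditional: "If descriptive analysis revealed the presence of potential confounding factors, appropriate multivariate analysis will then be considered". Section 9.5.3 gives the only stratification factor: "The randomization process will be stratified according to the delay from tracheal intubation to inclusion". Centre is not a stratum.

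**The concern.** A Ct is the cycle at which the signal crosses the threshold of one particular assay. It depends on extraction, gene target and platform as well as on the amount of virus. If laboratories differ in these, the same viral quantity gives different Ct values at different sites. A mean or median Ct per arm, pooled over sites, then has no common unit.

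Neither the planned test nor the randomisation accounts for laboratory, so shifts between laboratories pass into the error variance of the arm comparison. Reducing viral load is a stated secondary objective (7.2) and part of the trial's hypothesis. What is at stake is a real effect on Ct being missed, and a null result then being read as absence of antiviral activity.

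**Working it through.** The protocol gives no SD, effect size or power for viral load, so there is no figure of its own to reproduce. The size can only be shown as a range over assumptions.

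**From the protocol:** two-sided α of 5%; 250 per arm; at most 16 laboratories (16 centres); randomisation not stratified by centre; unadjusted t-test or Wilcoxon.

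**Assumed:** effect δ = 1.5 Ct; within-laboratory SD 5 Ct; between-laboratory SD s from 0 to 4 Ct; normal values; 180 or 150 measured patients per arm. The second figure matters at day 28. With the protocol's 40% control mortality, at most 250 × 0.60 = 150 controls are alive, so 180 per arm can apply only at earlier visits.

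**Formulae:** with r = s/5, the variance factor is 1 + r². The pooled SD is σ = √(25 + s²), and t-test power ≈ Φ(δ / (σ√(2/n)) − 1.96).

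Worked example, s = 3 and n = 180: r² = 9/25 = 0.36, so the factor is 1.36. Then σ = √34 = 5.83, the standard error is 5.83 × √(2/180) = 0.615, 1.5/0.615 = 2.44, and Φ(0.48) ≈ 68%.

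| s (Ct) | 1 + r² | t-test, formula, n = 180 | t-test, simulated, n = 180 | Wilcoxon, simulated, n = 180 | t-test, formula, n = 150 |
|---|---|---|---|---|---|
| 0 | 1.00 | 81% | 80% | 78% | 74% |
| 1 | 1.04 | 80% | 79% | 77% | 72% |
| 2 | 1.16 | 75% | 75% | 73% | 67% |
| 3 | 1.36 | 68% | 69% | 66% | 61% |
| 4 | 1.64 | 60% | 63% | 60% | 53% |

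The simulation draws 16 laboratory effects and assigns patients to arms without regard to laboratory. At large s it sits slightly above the formula, because 16 drawn laboratories have an expected spread of only 15/16 of s².

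**With laboratory as a factor in a linear model**, simulated power at 180 per arm is 78–81% for every s, and about 79–80% for s of 2 to 4. At s = 0 the model costs about 2 points (78% against 80%).

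**At 150 per arm**, simulated t-test power for s = 2, 3 and 4 is about 66%, 62% and 54%, against about 70% with laboratory as a factor. A repeat run gave 68%, 61% and 54%, against 71%, so the differences are simulation error.

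**Van Elteren test stratified by laboratory**, 180 per arm: about 75–77% at every s. At s = 0 to 1 that is slightly below the plain Wilcoxon test (77–78%). At s = 2 it is close to both planned tests. It gains clearly only at s = 3 or 4.

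**Type I error:** about 4.3–5.5% in simulations with r from 0 to 1, for the unadjusted and the adjusted tests alike.

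**The case against.** The strongest reply is that nothing here is invalid. Laboratory belongs to the site, not to the arm, so randomisation keeps the comparison unbiased. A reader might infer that chance imbalance of laboratories between arms makes the result misleading. That imbalance is ordinary sampling error and is already in the standard error, as the type I error near 5% confirms. This part of the reply stands in full.

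It also stands that the loss may be negligible. The protocol says nothing about how far laboratories differ, and at a between-laboratory SD of 1 Ct or less there is nothing to gain. A reader might also take 16 as the number of separate scales. It is the number of centres: hospitals may share a laboratory or platform, and the absence of calibration is inferred from the protocol's silence.

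A further reply is that adjustment is not excluded, because section 9.9 allows multivariate analysis and an analysis plan could add a centre term. That stands only in part. The clause depends on confounders appearing in descriptive analysis, and a laboratory shift unrelated to arm is not a confounder, so it would not trigger the clause. Meanwhile the protocol names an unadjusted test for this endpoint. Centre is known for every patient, so a proxy for laboratory survives; platform and gene target appear in none of the visit lists.

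Finally, the flow chart marks a viral load on day 1, and adjusting for it would remove part of a stable laboratory shift. But the endpoint and the test in 9.9 use the value at each visit.

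**Conclusion.** The point holds as one of efficiency and interpretability on a secondary endpoint. Assay, scale and test are all fixed in the protocol, and a better test is available at almost no cost. The unadjusted comparison is valid. It gives up precision by the factor 1 + r², with r unknown.

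Under the stated assumptions at 180 per arm, the loss against a laboratory-factor model runs from nothing (SD 0–1 Ct) to roughly 4–5, 10–11 and 16–17 points of t-test power at SD 2, 3 and 4 Ct. These figures rest on an assumed effect, an assumed within-laboratory SD and normal values; undetectable samples are not modelled. The documents do not support a reading that the viral-load result would be biased, that a power loss of known size is certain, or that the primary analysis of day-28 mortality is touched.

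**What to change.** In section 9.9, take Ct out of the list for the unadjusted t-test or Wilcoxon test. State that Ct at each visit will be compared between arms by a linear model with arm and laboratory as factors, with centre standing in where laboratory is unknown and very small centres pooled by a rule set beforehand. Report the within-laboratory arm difference with its confidence interval, rather than a pooled mean Ct per arm alone. Record laboratory, platform and gene target with each Ct. Keep a van Elteren test as a fallback only, since with up to 16 small strata it gives up power when laboratories agree.

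The cost is one sentence of analysis text, one CRF field and at most 15 degrees of freedom (16 laboratories − 1). If laboratories agree perfectly, the price is about 2 points of power. No extra samples are needed.

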| Study Design (Treatment Schema): Randomized open label trial                                                                                                                                                                                                                                                                                                                                                                                                                                                                                                                                                                                                                                                                                                                                                                                                                                                                                                                                                                                                                                                                                                                                                                                                                                                                                                                                                                                                                         |

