#### **9.4.4 No blinding**

We chose not to blind the treatments because the principal endpoint (day 28 mortality) is an objective one.

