#### **9.5.4.9 Assessment visit Day 365 (+- 30 days)**

- Vital status (dead/alive)
- Body weight
- Return to work (Y/N)
- ADL scale

- Anxiety depression scale
- EQ-5D-5L scale

This visit will be performed by phone call or by courier.

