#### **9.5.12 Assessment visits in case of discharge before day 90**

In case of acute care hospital discharge before day 90, the day 90 visit will be performed by phone call.

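### The reason for not blinding covers only day-28 mortality, and nothing provides for masking the assistant who collects ADL, anxiety-depression and EQ-5D-5L

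*Protocol*

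**What the plan says.** The synopsis (Protocol section 3) describes the design as "Study Design (Treatment Schema): Randomized open label trial". Section 9.4.4 gives the only reason: "We chose not to blind the treatments because the principal endpoint (day 28 mortality) is an objective one".

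Section 7.3 lists the ADL score, the anxiety-depression scale and EQ-5D-5L at days 90 and 365 as secondary endpoints. Section 9.6.1 has one designated person gather all three, in its words "by a clinical research assistant dedicated to this task by the coordinating center", at the day-90 visit and by telephone at day 365. The same section says of measurements in general: "Measurements will be performed by the investigators and clinical research assistants during their stay in the hospital and during medical visits".

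On the mode of contact, section 9.5.12 adds: "In case of acute care hospital discharge before day 90, the day 90 visit will be performed by phone call". For day 365, section 9.5.4.9 says: "This visit will be performed by phone call or by courier".

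No section says whether the dedicated assistant will be masked. The only other mention of a blind is a reporting item in section 10.1, on whether it was broken. That item does not fit an open-label trial and masks nobody.

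**The concern.** The argument in section 9.4.4 is sound for death at day 28, but it does not carry over to scales that depend on judgement or self-report. Someone who knows the arm can probe, prompt or resolve a borderline answer differently without intending to. These scales are how the trial assesses one of its stated secondary objectives, on functional and psychological state and quality of life (section 7.2).

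This is a matter of conduct. If scores are collected with knowledge of the arm, no later analysis can separate interviewer influence from treatment effect. It is therefore for the protocol to settle and cannot be left to an analysis plan. Section 9.4.4 took up blinding and closed the question with an argument that fits only one endpoint.

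**Working it through.** The point rests on reading the sections together; masking an assessor changes no sample size, power or alpha. The calculation in step 4 is illustrative.

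**1. Does the stated reason reach these endpoints?** Section 9.4.4 appeals to the objectivity of mortality. The three scales are not objective in that sense, so the choice not to blind is left unjustified for them.

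**2. Where could an interviewer influence the score?**
- ADL (Appendix C): six activities, each scored 1 or 0 according to whether help is needed. By phone, the interviewer turns a description into the point. Exposure is greatest here.
- Anxiety-depression (Appendix D) and quality of life (Appendix E): both are tick-box forms for the patient. Interviewer influence enters if they are read out by phone.
- Day 365 by courier (section 9.5.4.9): a self-completed form may involve no interviewer. Section 9.6.1 mentions only the phone for day 365.
- Day 90: by phone after discharge from acute care. Section 7.3 allows for patients still in an acute care hospital at that time, where the arm may be visible in the record.

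**3. Is masking practicable?** Section 9.6.1 already dedicates a person to the task. Treatment is a single administration (section 9.5.14), and section 9.5.2 expects most patients to be sedated or confused at inclusion, so many may not know their arm. Section 9.5.2 also has recovered patients asked to consent to continue, and some may learn their arm then. Masking would be partial.

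**4. How sensitive would a test be to a small shift?** Inputs from section 9.9: 250 per arm, 40% control mortality, an absolute reduction of 13.5 points, two-sided alpha 5%.
- Survivors at day 28: control 250 × 0.60 = 150; plasma 250 × (1 − 0.265) = 183.75, about 184; total 334.
- Standard error of a mean difference in SD units: √(1/150 + 1/184) = 0.110.
- Assumed shift 0.1 SD: 0.1/0.110 = 0.91 SE. With no true effect, the two-sided rejection probability is Φ(−1.96 + 0.91) + Φ(−1.96 − 0.91) = 0.149.
- Assumed shift 0.2 SD: 0.2/0.110 = 1.82 SE, giving 0.444.
- Shift 0: 0.05.

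The shifts come from no source. The survivor counts use day-28 mortality; later deaths and non-response would reduce them and somewhat lower the two probabilities. Section 9.9 names a test only for ADL and anxiety-depression at day 90, so the illustration applies directly only to those.

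**The case against.** The strongest reply is that the protocol is silent and not wrong. Section 9.4.4 concerns the treatments, no section gives the assistant access to allocation, and eCRF permissions and call scripts can sit in operational documents. It is true that the text is silent. A reader might infer from the open-label design that the assistant is unmasked, but the documents do not say so. The point still stands in its limited form: the protocol dealt with blinding, gave a reason confined to mortality, and assigned subjective endpoints to a named role without any safeguard.

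A second reply is that the bias is narrower than it looks. Two of the three instruments are self-report forms, courier returns may involve no interviewer, and patients are not masked, so their own reporting bias would survive any change. This also stands. A reader might infer that every day-90 and day-365 patient-centred endpoint is biased. The documents support only that bias is possible, mainly for ADL and for scales given by phone, and only if the assistant knows the arm and is influenced by it.

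A third reply is that masking may be harder than it appears. The wording may mean only that the coordinating center assigns the person, and an assessor at the bedside or with the patient's record is hard to mask. It would therefore be wrong to say that masking is free. It looks inexpensive for phone contacts, and less reliable for patients still in hospital at day 90.

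**Conclusion.** The point holds as an avoidable gap in conduct affecting secondary endpoints. The protocol's reason for not blinding does not extend to ADL, anxiety-depression and EQ-5D-5L, and nothing provides for masking the person who collects them. Day-28 mortality is unaffected.

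The size of any bias is unknown. The figures of 15% and 44% follow correctly from assumed shifts of 0.1 and 0.2 SD and the planned survivor counts. They show that a modest interviewer effect would matter at this sample size. A reader might take them as an estimate of the bias, and they are not one: the documents contain nothing on how large a shift to expect, and zero is possible. The change is a low-cost improvement and not a condition for the trial's main conclusion.

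**What to change.** Amend section 9.6.1 to state that the assistant collecting the three scales:
- has no access to allocation, through an eCRF role without the arm field;
- asks the patient at the start of each contact not to mention the treatment received;
- records whether the arm was nevertheless disclosed.

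Add to section 9.4.4 that its argument covers mortality only, and that patients' own reporting of these scales remains unmasked.

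The cost is a permission setting, a line of script and one extra data field. No visit, treatment or sample size changes, and the assistant is already planned. Masking will fail for some patients, especially those still in hospital at day 90, and patient reporting bias is not removed. The disclosure record at least lets the report say how often masking held.
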